#### Outcome Measures

In this trial, both primary and secondary outcomes will be assessed at baseline, upon intervention completion (week 12), and during the 12-week follow-up period (week 24).

#### Primary Outcome: Montreal Cognitive Assessment

The Montreal Cognitive Assessment (MoCA) [31] tests key areas such as executive function, verbal fluency, orientation, calculation, abstract thinking, delayed recall, visual perception, naming, attention, and concentration. A systematic review [32] indicates that the MoCA effectively detects MCI. Furthermore, the MoCA is a straightforward, independent cognitive screening tool with superior sensitivity (100%). Its memory test encompasses more words, fewer learning trials, longer recall delays, and a shorter assessment duration, rendering it appropriate for clinical applications. It demonstrates excellent test-retest reliability and positive and negative predictive values for MCI and AD [31]. Therefore, we used the MoCA test as our primary outcome measure to ensure maximum diagnostic accuracy.

#### Secondary Outcomes

##### Mini-Mental State Examination

The Mini-Mental State Examination (MMSE) [33] is a comprehensive 30-question assessment tool evaluating cognitive functions, including attention and orientation, memory, registration, recall, computation, language abilities, and the capacity to draw complex polygons [34]. However, an increasing number of studies indicate that the MMSE’s effectiveness in clinically detecting MCI is limited [34-36]. This implies that the MMSE is insufficient for identifying subtle cognitive changes in patients with MCI, particularly in cases of dementia without significant memory decline [34]. Consequently, in this study, the MMSE scale was used as a secondary outcome measure, complementing the MoCA scale to minimize the occurrence of false positives.

##### Blood Pressure Condition

Blood pressure measurements both in the clinic and through ambulatory monitoring were included. Clinic-based blood pressure measurement has primarily relied on the auscultatory method, using mercury, aneroid, or hybrid sphygmomanometers. Patients are advised to abstain from smoking, consuming caffeinated beverages, or exercising for 30 minutes before the measurement of their blood pressure [37]. In the clinic, at least 2 blood pressure readings will be obtained with an interval of 1 to 2 minutes, and the average of these readings will be considered. Should the difference between the first and second blood pressure readings exceed 10 mm Hg, a third measurement is advised, with the average of the latter 2 readings being taken.

The monitor should be fitted only after the patient has been in a relaxed state for at least 5 minutes. Blood pressure is subsequently measured in both arms, and an appropriately sized cuff is placed on the nondominant arm should the difference in systolic blood pressure be less than 10 mm Hg. In addition, an automatic noninvasive portable 24-hour dynamic blood pressure monitor will be attached to the nondominant arm for measuring brachial artery blood pressure. The monitoring frequency typically ranges from every 15 to 30 minutes during the day to every 30 minutes at night. The health care provider will instruct the patient to ensure that the monitor remains connected, to continue performing normal daily activities, and to keep the monitor arm stable and level with the heart throughout the 24 hours. A valid 24-hour ambulatory blood pressure monitoring session necessitates at least 14 readings during the day and at least 7 readings at night [38]. The computer will automatically calculate and record the following parameters: 24-hour mean systolic blood pressure, 24-hour mean diastolic blood pressure, daytime mean systolic blood pressure, daytime mean diastolic blood pressure, night mean systolic blood pressure, night mean diastolic blood pressure, along with the white coefficient of variance (defined as the ratio of the SD of blood pressure to the average systolic and diastolic blood pressure in the same time period) for daily and nocturnal systolic and diastolic blood pressures.

##### Verbal Fluency Test

Impaired executive function represents a principal manifestation of cognitive impairment related to hypertension. The Verbal Fluency Test demonstrates sensitivity in differentiating various cognitive impairments, with varying scores distinguishing between cognitively normal individuals and those exhibiting patterns of AD or MCI. Both in clinical and experimental contexts, the Verbal Fluency Test is extensively used for the diagnosis and assessment of a variety of neurological disorders [39].

##### The Shape Trail Test

The Shape Trail Test (STT) is a variant of the original Trail Making Test, known for its sensitivity in evaluating visual search and sequencing abilities, and is applied in cognitive function assessments. This study predominantly uses the STT, comprising 2 components, A and B. The STT-A assesses language and attention capabilities, whereas the STT-B focuses more extensively on executive function and memory [40].

##### Auditory Verbal Learning Test

The Verbal Learning Test is considered the most reliable predictor of the transition from MCI to AD. In this study, the primary tool used is the Auditory Verbal Learning Test–Huashan version. This version uses the principles and methods of the California Verbal Learning Test, a standardized Verbal Learning Test, and comprises both short-term and long-term delayed recall, making it apt for detecting cognitive impairment in patients with impaired memory [41].

##### Activity of Daily Living

Activities of Daily Living (ADL) are an effective instrument for dementia screening and are well-suited for assessing the daily functional abilities of patients with MCI [42]. This study predominantly uses ADL to diagnose hypertension-related cognitive impairment, encompassing both basic ADL and instrumental ADL. The former pertains to the fundamental skills necessary for independent living, while the latter involves capabilities for more complex daily and social activities [43].

##### Hamilton Anxiety Scale and Hamilton Depression Scale

This scale also serves to assess the anxiety or depression status of the participants over the past week, using a combination of conversation and observation. Research has indicated that cognitive impairment is bidirectionally associated with higher anxiety and depression scores. In this study, the Hamilton Anxiety Rating Scale and the Hamilton Depression Rating Scale will be used to assess hypertension combined with cognitive impairment [44].

##### Pittsburgh Sleep Quality Index

Sleep disorders are known to contribute to various metabolic disorders, including obesity, diabetes, and dyslipidemia, all of which are key factors in high blood pressure [45]. The Pittsburgh Sleep Quality Index evaluated sleep quality through 7 aspects: sleep quality, time to fall asleep, sleep duration, sleep efficiency, sleep disturbance, use of hypnotic drugs, and daytime dysfunction [46].

##### Transcranial Doppler

Transcranial Doppler (TCD) is a useful tool in the diagnosis and treatment of clinical cerebrovascular diseases. In particular, TCD can be used to assess the effects of cerebral artery stenosis and occlusion on cerebral hemodynamics [47]. Hypertension is the major vascular risk factor for cerebral small vessel disease. TCD is a noninvasive method that allows the monitoring of microvascular hemodynamic functional integrity to help guide therapies aimed at the cerebral microcirculation and neurovascular unit [48]. At the same time, studies have shown that cerebral hypoperfusion is associated with both cognitive decline and white matter lesions. Therefore, TCD can explore the cognitive impairment in the midbrain hemodynamic and small vessel disease caused by the relationship between the brain lesions [49]. Important parameters measured in this study include the mean velocity, resistance index, and pulse index within both cerebral arteries.

##### Microcirculation-Related Palliation

The microcirculation, often regarded as a hidden organ, consists of the smallest blood vessels, including resistance arterioles, capillaries, and venules [50]. The endothelium mediates the vasomotor tone of the microcirculation through the release of vasodilators (such as nitric oxide [NO]) and vasoconstrictors (such as endothelin-1 [ET-1]). Concurrently, impaired vasodilation, mediated by reduced NO production, is a characteristic feature of endothelial dysfunction [51]. Consequently, NO and ET-1 will be used as biomarkers to assess microcirculation indicators in patients.

### Safety Evaluation

Adverse reactions, including needle-sickness, needle stagnation, needle bending, broken needle, and subcutaneous hematoma, will be closely monitored during the treatment process. Concurrently, a detailed analysis will be conducted on the correlation between all adverse events and acupuncture to rigorously evaluate the safety of acupuncture treatment. All adverse events will receive appropriate intervention, and serious adverse events will be reported to the ethics committee immediately.

### Data Management and Quality Control

Quality control will be implemented for all records of clinical trials, including case reports, needling operation lists, blood pressure monitoring forms, cognitive assessment scales, among others, with strict control of the time window for follow-up collection to ensure that the data are accurate, complete, truthful, and timely. These records shall not be omitted or arbitrarily altered.

A specialized quality control team will be established to conduct regular on-site inspections. Simultaneously, a comprehensive quality control system will be established during the implementation of the project, and we will formulate a series of standard operating procedures, including standard operating procedures for the study process, the acupuncture treatment, and the follow-up assessment. Furthermore, the Data Inspection Committee has been commissioned to regularly review and assess the data accumulated from the clinical trials, thereby evaluating the quality, efficacy, and safety of the trials.

### Sample Size

According to the literature [52], acupuncture treatment increased the mean MoCA score by 2.83 (SD 1.13); the mean change in MoCA in the sham acupuncture group was 1.97 (1.38), waiting group, the mean change in MoCA was 0.48 (SD 1.65); the test level was α=0.01; power was 95%; and it was calculated by the PASS (version 15.0; NCSS, LLC) software to obtain a sample size of 66, considering a 20% dropout rate, 84 cases were proposed to be included in each group, and 252 participants were finally included.

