### Statistical Analysis

Statistical analysis was performed using SPSS (version 27.0) software. All patients who completed the randomization and received the overall course of treatment were included in the efficacy analysis to ensure the integrity and comparability of the data. For different types of data, the following statistical methods will be used for analysis:

Data types and test methods: ×2 test is used for count data, and Shapiro-Wilk and Levene test are used for measurement data to analyze the independence, normality, and homogeneity of variance of data.Comparison between groups: for normal distribution and homogeneity of variance, 1-way ANOVA with completely random design was used for comparison between groups. If the variance is not uniform, the Kruskal-Wallis rank sum test of the single-factor nonparametric method of completely random design is used for comparison between groups. For the measurement data conforming to the skewed distribution, the Kruskal-Wallis rank sum test of the single-factor nonparametric method of completely random design was used for comparison between groups.Hypothesis testing and significance level: The count data are expressed as a ratio (%) using the chi-square test or Fisher exact test. The 2-sided test method was used uniformly, and the test statistics and corresponding *P* values were recorded. *P*<.05 was used as a criterion for judging significant statistical significance.

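### Sample Size sets alpha at 0.01 but Statistical Analysis judges at two-sided P<.05, and the 66 carried forward as a per-group number does not follow from the stated inputs

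*Protocol article*

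**What the plan says.** The Sample Size section of the protocol article gives mean MoCA changes and SDs for all three arms and then the design values: "the test level was α=0.01; power was 95" per cent. It reports that PASS was used "to obtain a sample size of 66, considering a 20% dropout rate, 84 cases were proposed to be included in each group", for 252 in all. It does not name the test or comparison that was sized, does not say whether that test was one- or two-sided, and does not label the 66 as per group or total. Because 66 is inflated straight to 84 per group, it is used as a per-group figure.

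The Statistical Analysis section plans a one-way ANOVA across the three groups, or Kruskal-Wallis where its assumptions fail. It adds "The 2-sided test method was used uniformly" and, for the P value, "<.05 was used as a criterion for judging significant statistical significance". It mentions no 0.01 level and no separate test of electroacupuncture (EA) against sham electroacupuncture (SEA).

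**The concern.** The article fixes two different significance levels and does not reconcile them. A primary MoCA result with P between .01 and .05 would be a success under Statistical Analysis and a failure at the test level in Sample Size. This is not detail left to a fuller document, because both levels are printed here.

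The sample-size statement also does not hold together. Alpha 0.01, 95% power and 66 per group should describe one calculation on the stated means and SDs. If they do not, a reader cannot tell what the trial was designed to detect, or how much power the sham-controlled contrast has. That contrast is the one that separates a specific needling effect from the effect of attending for treatment.

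**Working it through.** **Inputs (Sample Size section, change in MoCA)**

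| Arm | Mean | SD | Variance |
|---|---|---|---|
| EA | 2.83 | 1.13 | 1.2769 |
| SEA | 1.97 | 1.38 | 1.9044 |
| Waiting list | 0.48 | 1.65 | 2.7225 |

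Alpha is 0.01, power 95% and dropout 20%. Two-sided testing comes from Statistical Analysis.

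**1. Dropout step.** 66/(1 − 0.20) = 82.5, so 83; the article says 84. In the other direction, 84 × 0.80 = 67.2 evaluable. The difference of one patient is immaterial, and the step confirms that 66 is treated as per group.

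**2. EA versus SEA, two-sided 0.01.** The difference is 2.83 − 1.97 = 0.86, and the variances sum to 1.2769 + 1.9044 = 3.1813.

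- Normal approximation for 95% power: n = (2.576 + 1.645)² × 3.1813/0.86² = 76.6, so 77 per group. The noncentral t gives 79.
- Power at 66 per group: SE = √(3.1813/66) = 0.2196, and 0.86/0.2196 = 3.917. The normal approximation gives Φ(3.917 − 2.576) = 91.0%; the noncentral t (Welch) gives 90.1%.
- At two-sided 0.05 with the same n, the normal approximation gives Φ(3.917 − 1.960) = 97.5%; the noncentral t gives 97.3%.
- One-sided 0.01 at 66 per group gives 93.9%, still short of 95%, and Statistical Analysis excludes one-sided tests.

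**3. Other pairs, two-sided 0.01, 95% power.** EA versus waiting list needs 15 per group, and SEA versus waiting list needs 39. EA versus SEA is therefore the most demanding pair.

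**4. Three-group F test, alpha 0.01, 95% power.** The grand mean is (2.83 + 1.97 + 0.48)/3 = 1.76. The squared deviations are 1.07² + 0.21² + 1.28² = 2.8274. The noncentrality is λ = n × 2.8274/SD².

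- Pooled SD = √(5.9038/3) = 1.403: n = 16 per group (λ = 22.99), a total of 48.
- SD 1.65, the largest stated value and an assumed choice: n = 22 per group (λ = 22.85, power 95.6%), a total of 3 × 22 = **66**.
- At 66 per group with SD 1.65, λ = 68.5 and power exceeds 99.99%.

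**5. Which readings return 66?**

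| Reading | Matches 66? | What has to change |
|---|---|---|
| EA vs SEA, two-sided 0.01, 95%, per group | No (77 to 79) | – |
| EA vs SEA, two-sided 0.01, 90%, per group | Yes (65 to 66) | Power is 90%, not 95% |
| EA vs SEA, two-sided 0.025, 95%, per group | Close (65 to 67) | Alpha is not 0.01 |
| Three-group F test, 0.01, 95%, SD 1.65 | Yes, as a total | 66 is not per group |

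No two-sided reading tried gives 66 per group at both stated values, alpha 0.01 and 95% power.

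**The case against.** The strongest reply is that the article never attaches its 95% to EA versus SEA. It lists all three arms and plans a three-group ANOVA, for which 66 per group is far more than enough. A reader might infer that the trial is underpowered for the sham comparison; the documents do not support that. The 90% figure arises only if the reader supplies both the contrast and the 0.01 rule, and the analysis section does not apply 0.01. Under the rule it does apply, EA versus SEA has 97.3% power at 66 per arm. This part of the reply stands.

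A reader might also infer that the false-positive rate is inflated fivefold. That is only the ratio 0.05/0.01 of two nominal levels, and 5% two-sided is a conventional choice. Sizing at a stricter level than is later tested is conservative for power.

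It can further be said that an article may leave the details of a PASS run to the full protocol. That is fair for omitted details. It does not cover two conflicting alphas, or a per-group number that its own printed inputs do not return.

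Finally, the match between 66 and an ANOVA total depends on choosing SD 1.65, and the other readings in the table come as close by changing alpha or power. The explanation that a total was carried forward is therefore plausible, not established.

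**Conclusion.** The conflict between alpha 0.01 and two-sided P<.05 is certain from the text, and it decides how a primary result with P between .01 and .05 is classified. It has to be corrected.

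It is also shown that 66 per group does not follow from the stated means and SDs at two-sided 0.01 and 95% power. EA versus SEA would need about 79 per arm and has about 90% at 66; the ANOVA needs 16 to 22 per group, depending on the SD. These figures assume approximately normal changes, the arm-specific SDs for the pairwise test, and either the pooled SD or 1.65 for the F test.

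The documents do not show that the trial is too small, that EA versus SEA was the contrast sized, or which slip produced the 66.

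**What to change.** Make three changes of wording before unblinding. The Results section says that no analysis has been performed, so on the article's own account there is still time.

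1. Use one alpha for the primary MoCA analysis in both Sample Size and Statistical Analysis. It should be the level that was prespecified, with documentation, and not one chosen now.
2. State from the PASS record which test and comparison were sized, with which SD and sidedness, and whether 66 was per group or a total. EA versus SEA should be named as the sized contrast only if the record shows it.
3. Restate the power that 66 evaluable per arm gives, including for EA versus SEA: about 90% at two-sided 0.01, or about 97% at two-sided 0.05.

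The sample size stays at 84 per group and 252 in all. The only cost is that the stated power for the sham contrast looks slightly less favourable if 0.01 is kept.

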### Statistical Analysis

Statistical analysis was performed using SPSS (version 27.0) software. All patients who completed the randomization and received the overall course of treatment were included in the efficacy analysis to ensure the integrity and comparability of the data. For different types of data, the following statistical methods will be used for analysis:

Data types and test methods: ×2 test is used for count data, and Shapiro-Wilk and Levene test are used for measurement data to analyze the independence, normality, and homogeneity of variance of data.Comparison between groups: for normal distribution and homogeneity of variance, 1-way ANOVA with completely random design was used for comparison between groups. If the variance is not uniform, the Kruskal-Wallis rank sum test of the single-factor nonparametric method of completely random design is used for comparison between groups. For the measurement data conforming to the skewed distribution, the Kruskal-Wallis rank sum test of the single-factor nonparametric method of completely random design was used for comparison between groups.Hypothesis testing and significance level: The count data are expressed as a ratio (%) using the chi-square test or Fisher exact test. The 2-sided test method was used uniformly, and the test statistics and corresponding *P* values were recorded. *P*<.05 was used as a criterion for judging significant statistical significance.

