### Waiting List Group

No acupuncture treatment will be given in the waiting list group for the first 12 weeks. Participants will be required to complete the assessments at the corresponding time points. Considering the ethical requirements, compensatory treatment will be given after 12 weeks of following up.

The specific flowchart is shown in Figure 1.

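### The only stated efficacy set is completers, selected after randomisation, and the completion criterion has no defined meaning in the waiting-list arm

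*Protocol article*

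**What the plan says.** The Statistical Analysis section states who enters the efficacy analysis: "All patients who completed the randomization and received the overall course of treatment were included in the efficacy analysis". It gives data integrity and comparability as the reason. The article names no other efficacy population, and no intention-to-treat or full analysis set.

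The Sample Size section allows for loss: "considering a 20% dropout rate, 84 cases were proposed to be included in each group", starting from a calculation run "to obtain a sample size of 66".

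Trial Design and the Electroacupuncture Group section set three sessions a week for 12 weeks, which is 3 × 12 = 36 sessions. The sham arm has the same number and frequency. For the third arm, the Waiting List Group section says: "No acupuncture treatment will be given in the waiting list group for the first 12 weeks". Compensatory treatment follows later. Under Interventions, all three groups also receive standard treatment. What counts as the overall course is not said for any arm.

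**The concern.** The rule joins two conditions: being randomised, and having received the overall course. The second is an outcome of the trial. Patients who stop a 36-session course early may differ from those who finish, and the reasons may differ between arms, because electroacupuncture involves Deqi and current while sham is shallow needling without current. Comparability comes from the 1:1:1 randomisation, and conditioning on completion gives part of it away.

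The criterion also does not carry over to the waiting list. Two arms are screened on attending a long course of sessions, and the third is screened on something unstated or on nothing.

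At stake is the primary MoCA comparison. The Conclusions section speaks of efficacy in hypertension with cognitive impairment, whereas this set would support a statement about completers only. Because the article fixes the set in words, this is not a detail left to an analysis plan: a plan that follows the sentence inherits the problem, and one that uses all randomised patients contradicts it.

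**Working it through.** **Inputs from the Sample Size section.** MoCA change: electroacupuncture 2.83 (SD 1.13), sham 1.97 (SD 1.38), waiting list 0.48 (SD 1.65). Planned difference between electroacupuncture and sham: 2.83 − 1.97 = 0.86. Size 66 before dropout (read as per group), dropout 20%, 84 per group, 252 in total.

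**1. The plan's own figure.** 66 / (1 − 0.20) = 82.5, so 83 per group. The stated 84 is one more and is accepted as reproduced.

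**2. How many could be excluded.** If non-completion equals the planned dropout:
- 0.20 × 252 = 50.4, about 50 patients excluded;
- 0.80 × 84 = 67.2 per group remain, about 202 in all.

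If exactly 66 per group remain, 3 × (84 − 66) = 54 are excluded, and 54 / 252 = 21.4%.

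**3. Is loss of numbers the problem?** The SD averaged on the variance scale is √((1.13² + 1.38²)/2) = 1.261. At two-sided α = 0.01, power for electroacupuncture against sham is about 90–91% with 66–67 per group and 96–97% with 84. The size was inflated for this loss, so the issue is selection and not mainly precision.

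**4. Size and direction of the bias (illustration; the loss model is assumed).** Let z be a patient's standardised response, with no true difference between arms. The probability of exclusion is 1 / (1 + exp(−(a − b·z))), with a set so that 20% of each arm is excluded. The completer mean of z is ∫ z(1 − p(z))φ(z)dz / 0.80, which equals 0.096, 0.173 and 0.227 SD for b = 0.5, 1.0 and 1.5.

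| Loss depends on response in | Apparent electroacupuncture − sham difference, MoCA points |
|---|---|
| Electroacupuncture only, SD 1.38 | +0.13, +0.24, +0.31 (15% to 36% of 0.86) |
| Electroacupuncture only, SD 1.13 | +0.11, +0.20, +0.26 (13% to 30% of 0.86) |
| Both, sham slope half, SD 1.38 | +0.06 to +0.12 |
| Both, same slope, common SD | 0 |
| Both, same slope, SDs 1.13 and 1.38 | −0.02 to −0.06 |
| Sham only, SD 1.38 | −0.13 to −0.31 |

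**5. The same question from observed completers.** Suppose completers show 0.86 and 20% are excluded in each arm. With excluded patients changing by x (electroacupuncture) and y (sham), the all-randomised difference is 0.80 × 0.86 + 0.20 × (x − y) = 0.688 + 0.20(x − y).
- x = 0.48, y = 1.97: 0.688 − 0.298 = 0.39
- x = y = 0.48: 0.69
- x = 2.83, y = 0.48: 0.688 + 0.470 = 1.16

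**6. What the rule means in the waiting-list arm.**
- If treatment means acupuncture, no waiting-list patient has had a course by the week-12 assessment, and the arm would be empty there.
- If it means standard treatment, the filter is far weaker than 36 sessions.
- If it means the compensatory treatment, membership in the week-12 analysis would depend on something that happens after week 12.

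The text does not choose between these. On none of them do the three arms pass through the same filter.

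**The case against.** The strongest reply is that the figures attached to this point can easily be pushed too far. Much of that stands.

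- A reader might infer that one randomised patient in five will be dropped. The documents do not say so. The 20% is a planning allowance for dropout, not a rate of failing to finish the course. Patients who stop sessions but are still assessed would be excluded without being dropouts, and patients lost after week 12 may have finished the course.
- A reader might infer that the waiting-list arm cannot meet the rule and so disappears. That is not shown either. All arms receive standard treatment, the waiting list is treated later, and the Conclusions section keeps it as a comparator. What the text supports is that the criterion is undefined there and works unequally.
- A reader might infer that the rule favours electroacupuncture. That needs loss to depend on response more strongly in that arm. Nothing in the article establishes this, and the sham arm carries the same visit burden. Equal dependence gives about zero.

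It can also be said that the sample size already allows for dropout. That protects power but does nothing about who is left. None of these replies alters the sentence itself: it names a completer set, and nothing else in the article overrides it.

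**Conclusion.** The statement is wrong as written and should be changed before any analysis. The sole efficacy population is selected on an event after randomisation, with a criterion that has no defined meaning in one of three arms.

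The size cannot be known from the document. If non-completion matches the planned 20%, about 50 of 252 are excluded. Under the assumed loss models the bias in electroacupuncture against sham runs from about −0.31 to +0.31 MoCA points, set against a planned 0.86. The extremes need response-dependent loss in one needled arm only, with b = 1.5 and SD 1.38. The direction cannot be fixed in advance, so the rule can bias the primary comparison, but a bias in favour of treatment is not established.

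**What to change.** Replace the sentence with wording such as: *The primary efficacy analysis includes all randomised participants in the arm to which they were randomised, regardless of sessions received, using all MoCA data collected.*

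Keep the full-course set as a per-protocol sensitivity analysis, and state for each arm, including the waiting list, what completion means.

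The Results section says both that collection ended in April 2025 and that it is still under way. Where it is open, continue MoCA assessments after a patient stops sessions. Where it has closed, use what was collected from those patients. A likelihood-based repeated-measures model is one way to use partial data, but the correction does not depend on it.

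The cost is one sentence, a definition per arm and slightly more analysis work. The estimated effect may turn out smaller. The article reports that no analysis has been done, so the change can still be made in advance.

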### Conclusions

This clinical trial aims to compare the efficacy of electroacupuncture versus SEA or waiting list control in the treatment of hypertension with cognitive impairment and to explore its impact on microcirculation through hemodynamic and microcirculatory indices. The results of this trial will contribute to clarifying the microcirculatory mechanisms of electroacupuncture in the treatment of hypertension with cognitive impairment, providing a solid foundation for further research on electroacupuncture therapy.

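### The only efficacy test stated for MoCA is a three-group omnibus test, which cannot show that electroacupuncture beats sham

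*Protocol article*

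**What the plan says.** The Statistical Analysis section of the protocol article sets the between-group comparison for measurement data. Under normality and equal variances, "for normal distribution and homogeneity of variance, 1-way ANOVA with completely random design was used for comparison between groups". Otherwise, "If the variance is not uniform, the Kruskal-Wallis rank sum test of the single-factor nonparametric method of completely random design is used"; the same rank test applies to skewed data. On sidedness, "The 2-sided test method was used uniformly", and the significance threshold is .05. The section names no comparison between two particular arms. The article's only two-sample t test is under Baseline Comparability.

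The Conclusions, in both the abstract and the discussion, give the aim: "This clinical trial aims to compare the efficacy of electroacupuncture versus SEA or waiting list control". The primary outcome is the change in MoCA. Under Outcome Measures, "both primary and secondary outcomes will be assessed at baseline, upon intervention completion (week 12), and during the 12-week follow-up period (week 24"), and neither post-baseline visit is marked as primary.

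The Sample Size section plans on "acupuncture treatment increased the mean MoCA score by 2.83 (SD 1.13"), a change of 1.97 (SD 1.38) with sham and 0.48 (SD 1.65) on the waiting list. It adds that "the test level was α=0.01; power was 95"%, and arrives at 66 per group, raised to 84 for dropout.

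**The concern.** A significant F or Kruskal-Wallis test says that the three arms are not all alike. It does not say which arms differ. The sham arm is there to separate the effect of EA from that of being needled at all, and the stated test does not isolate that comparison.

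The planning values make this more than a formality. The assumed distance from sham to waiting list (1.97 − 0.48 = 1.49 points) is larger than that from EA to sham (2.83 − 1.97 = 0.86 points). The waiting list alone can therefore make the test significant. A trial in which EA adds nothing to sham would still produce a significant result on the only test that the section gives, and that result could be reported as evidence of efficacy.

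**Working it through.** **Inputs.** Means, SDs, α = 0.01, 95% power and 66 or 84 per group come from Sample Size; two-sided .05 comes from Statistical Analysis. For the F test I take a common variance: (1.13² + 1.38² + 1.65²)/3 = 5.9038/3 = 1.968, so SD 1.403.

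**1. The plan's own figure of 66.**
- *Omnibus ANOVA, α = 0.01, 95% power.* The grand mean is 1.76, and the sum of squared deviations is 1.07² + 0.21² + 1.28² = 2.827. The noncentrality is λ = n × 2.827/1.968. At n = 16, λ = 23.0 and power is 95%. The omnibus test thus needs 16 per group (11 to 22 for a common SD from 1.13 to 1.65).
- *EA versus SEA.* Pooled SD = √[(1.13² + 1.38²)/2] = 1.261. The two-sided normal formula gives n = 2 × (2.576 + 1.645)² × (1.261/0.86)² = 77 (79 with the t distribution). One-sided it gives 68 (70 with t).
- Neither route gives exactly 66 at 95% power; a two-sided t test at .01 gives 66 at 90% power. Still, 66 is far from the omnibus requirement and close to that of EA versus SEA.

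**2. The omnibus test when EA equals sham.** Put both needled arms at 1.97 and the waiting list a gap g below. The sum of squared deviations is then (2/3)g², and λ = n × (2/3)g²/1.968. At g = 1.49 and n = 66, λ = 66 × 1.480/1.968 = 49.6. Probability of P < .05 (noncentral F with 2 and 3n − 3 degrees of freedom):

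| Gap, points | λ at 66 per arm | 66 per arm | 84 per arm |
|---|---|---|---|
| 1.49 (planning) | 49.6 | >99.99% | >99.99% |
| 1.00 | 22.4 | 99.2% | 99.9% |
| 0.75 | 12.6 | 89.3% | 95.5% |
| 0.50 | 5.6 | 54.5% | 65.7% |
| 0.25 | 1.4 | 16.7% | 20.2% |

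At the planning gap the figure also exceeds 99.99% at α = 0.01. Simulation with the three unequal planning SDs (5,000 trials) had ANOVA and Kruskal-Wallis both rejecting in 100% of trials at that gap. At 66 per arm, simulation gave about 54% at 0.5 points and 18% at 0.25. Levene's test rejected in 69% of trials at 66 per arm and 80% at 84. Kruskal-Wallis is therefore the likelier route, and it has the same limitation.

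**3. The contrast that answers the question.** For EA minus SEA at 66 per arm, the noncentrality is 0.86/(1.261 × √(2/66)) = 3.92. Two-sided t-test power is 97.3% at .05 and 90.2% at .01. With 67 per arm (84 × 0.80 = 67.2) it is 97.5% and 90.7%. If EA equals sham, this contrast is falsely significant about 5% of the time at .05 (4.5% in simulation), whatever the waiting list does.

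**The case against.** The strongest reply is that a journal article condenses. Pairwise tests and a multiplicity rule may sit in a full protocol or analysis plan that is not shown, and a size of 66, near the EA-versus-SEA requirement, suggests that the designers had that contrast in mind. The section also does not say that a significant omnibus test will be read as EA beating sham. All of this stands as far as it goes: a missing post hoc method is not the point. But the article does not leave the test open. It states one, and that test does not match the stated aim.

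Two stronger readings are tempting, and the documents support neither.
- A reader might infer that unadjusted pairwise tests at two visits inflate the familywise error. The article contains no such tests. With three groups, pairwise tests run only after a significant omnibus test keep the familywise error near 5% at one visit (5.1% to 5.4% in simulation). In the scenario of step 2, moreover, only EA versus SEA is a true null.
- A reader might infer from the aim's wording that success against either control is enough. The phrase lists comparators; it is not a decision rule.

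It is also fair to say that week 12, the end of treatment, is the natural primary visit. It is just not designated.

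**Conclusion.** The point holds in this form: the omnibus test, which is all that the article states for MoCA, cannot by itself support a claim that EA is better than sham. That is a matter of logic and depends on no assumed number.

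The size does depend on assumptions. With EA equal to sham, near-certain significance rests on the article's planning means and SDs. It persists at a waiting-list gap of 1.0 point (about 99% at 66 per arm), but drops to about 54% at 0.5 and 17 to 18% at 0.25. It would therefore be too strong to say that the waiting list will make the test significant whatever the true gap.

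The mismatch between α = 0.01 in Sample Size and .05 in Statistical Analysis, and the failure to reproduce 66 at 95% power, are separate matters. They do not change this conclusion.

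**What to change.** In Statistical Analysis, name EA minus SEA in MoCA change at week 12 as the primary contrast. Report it with an estimate and confidence interval, and rest the efficacy conclusion on it. State the rule for EA versus waiting list: a fixed sequence after a significant primary contrast is one valid choice, and a Bonferroni split is another. Make week 24 secondary, and align the wording of the aim with this order. The omnibus test may stay as a supporting or gatekeeping test. State the one significance level that applies, since the two sections differ.

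The cost is a dated change of wording before unblinding; the Results section says that no analysis had been performed. No extra patients are needed: under the planning values, 66 per arm gives 97% power at two-sided .05 and 90% at .01. The 95% power quoted in Sample Size is thus met at .05 but not at .01, where it would take 79 per arm before dropout. The price is that no claim of efficacy beyond sham can rest on the omnibus test or on the waiting-list comparison alone.
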